**Fig. 3 Fig3:**
[figure not shown]
Stage 1 analysis of the impact of the nutritional interventions on DNA methylation

Statistical power is estimated based on a sample size of 700 in the Indian cohort and 293 in The Gambia, to detect DMPs at a single locus using two-sample t-tests with alpha = 0.05, using a conservative assumption that tested loci have a methylation standard deviation at the 95th percentile of those observed (ie. within the 5% most variable probes). Significance thresholds were Bonferroni-adjusted assuming 800,000 independent tests, allowing for some filtering of probes. We estimate that we will be able to detect mean methylation differences between intervention and control groups, with 80% power, of 3 and 5% in the Indian and Gambian cohorts respectively. For the replication study using pyrosequencing in independent samples from the Indian cohort, and in the candidate loci studies in both cohorts, we estimate 80% power to detect a 2% difference in the Indian cohort and 3% in the Gambian cohort.

*Stage 2: Methylation-outcome associations (*Figs. 4 and 5
*,* Table 4
*):* Significant loci associated with the nutritional intervention in either cohort from the EPIC array analysis, and all candidate loci, will be tested for associations with phenotype data measured in the children at the time of DNA collection, and also with birth outcomes (newborn anthropometry and gestation) (Table 4, Fig. 4). Loci identified in a separate meta-analysis of Stage 1 associations across both cohorts will also be considered. We will additionally carry out a ‘hypothesis-free’ analysis to identify loci where methylation is associated with outcomes, irrespective of intervention-methylation associations (Fig. 5).

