## Abstract

**Background:**

Animal studies have shown that nutritional exposures during pregnancy can modify epigenetic marks regulating fetal development and susceptibility to later disease, providing a plausible mechanism to explain the developmental origins of health and disease. Human observational studies have shown that maternal peri-conceptional diet predicts DNA methylation in offspring. However, a causal pathway from maternal diet, through changes in DNA methylation, to later health outcomes has yet to be established. The EMPHASIS study (Epigenetic Mechanisms linking Pre-conceptional nutrition and Health Assessed in India and Sub-Saharan Africa, ISRCTN14266771) will investigate epigenetically mediated links between peri-conceptional nutrition and health-related outcomes in children whose mothers participated in two randomized controlled trials of micronutrient supplementation before and during pregnancy.

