**Methods:**

The original trials were the Mumbai Maternal Nutrition Project (MMNP, ISRCTN62811278) in which Indian women were offered a daily snack made from micronutrient-rich foods or low-micronutrient foods (controls), and the Peri-conceptional Multiple Micronutrient Supplementation Trial (PMMST, ISRCTN13687662) in rural Gambia, in which women were offered a daily multiple micronutrient (UNIMMAP) tablet or placebo. In the EMPHASIS study, DNA methylation will be analysed in the children of these women (~1100 children aged 5–7 y in MMNP and 298 children aged 7–9 y in PMMST). Cohort-specific and cross-cohort effects will be explored. Differences in DNA methylation between allocation groups will be identified using the Illumina Infinium MethylationEPIC array, and by pyrosequencing top hits and selected candidate loci. Associations will be analysed between DNA methylation and health-related phenotypic outcomes, including size at birth, and children’s post-natal growth, body composition, skeletal development, cardio-metabolic risk markers (blood pressure, serum lipids, plasma glucose and insulin) and cognitive function. Pathways analysis will be used to test for enrichment of nutrition-sensitive loci in biological pathways. Causal mechanisms for nutrition-methylation-phenotype associations will be explored using Mendelian Randomization. Associations between methylation unrelated to supplementation and phenotypes will also be analysed.

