## Background

EMPHASIS (Epigenetic Mechanisms linking Pre-conceptional nutrition and Health Assessed in India and Sub-Saharan Africa, www.emphasisstudy.org) is a collaboration between investigators in the UK, India and The Gambia designed to profile genome-wide DNA methylation in children whose mothers participated in two pre- and peri-conceptional micronutrient supplementation trials (the Mumbai Maternal Nutrition Project in India, MMNP [1] and the Peri-conceptional Multiple Micronutrient Supplementation Trial, PMMST, in rural Gambia [2]). The main objectives of the study are to identify methylation differences associated with the interventions and correlate these with health-related phenotypes in the children, including size at birth, post-natal growth, and childhood body composition, skeletal health, cardiometabolic risk markers and cognitive function. We hypothesise that maternal nutritional supplementation around the time of conception will result in altered DNA methylation profiles in the children, and that the distinct methylation patterns identified will show potentially causal associations with phenotypic characteristics in the children. We further expect to identify methylation differences unrelated to supplementation that are associated with the measured phenotypes.

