There is evidence in humans that epigenetic changes induced by the nutritional environment in early life alter later phenotype, including body composition and cardiometabolic health. For example, DNA methylation at a number of loci (insulin-like growth factor 2 (*IGF2*), retinoid X receptor alpha (RXRA), endothelial nitric oxide synthase (*eNOS*), *PGC1α*, and cyclin-dependent kinase inhibitor 2 (*CDKN2a*) genes in cord tissue, cord blood or children’s leucocytes is associated with adiposity in later childhood [11–14]. Studies in The Gambia, where there is marked seasonal variation in maternal nutrition, have shown that season of conception is related to DNA methylation of human infant MEs [15], and that methylation is predicted by elements of the mother’s methyl donor metabolome at conception [16]. One implicated gene is the maternally imprinted tumour suppressor and immune function regulator vault RNA2–1 (*VTRNA2–1*) [17], making it a promising candidate for exploring mechanisms linking season of conception and infectious disease mortality in Gambians [18]. A methylation variant affecting expression of the pro-opio-melanocortin (*POMC*) gene has also been associated with child and adult obesity. This locus is an ME, and in Gambian infants methylation is associated with season of conception and maternal 1-carbon metabolites at conception [19].

Evidence for epigenetic programming in humans has hitherto relied mainly on observational studies. Randomised trials of peri-conceptional maternal nutritional interventions with follow-up of the children represent a stronger study design in which to examine effects on DNA methylation and health-related phenotypes, reducing the problems of confounding and bias that affect observational studies, thus providing stronger evidence of causality. The EMPHASIS study will be an important step towards understanding mechanisms underpinning the developmental origins of health and disease (DOHaD), identifying biomarkers of early life exposures associated with later disease risk, and designing more effective nutritional interventions for mothers preparing for pregnancy.

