### Data analysis

A detailed analysis plan can be found on the EMPHASIS website (www.emphasisstudy.org).

*Stage 1: Intervention-methylation associations (*Fig. 3
*):* Data from the two cohorts will be analysed separately. In a ‘hypothesis-free’, genome-wide analysis, the raw intensity data from the EPIC arrays will undergo pre-processing, quality control and normalization. Intervention-methylation associations will be identified at DMRs and DMPs using appropriate methods, and controlling for the false discovery rate (FDR). Loci and regions showing differences in methylation variance (VMPs and VMRs) will be identified, both genome wide and in an analysis targeted to MEs and imprinting control regions (ICRs). The candidate gene data will be analysed in parallel, using a similar strategy to the one outlined above to identify methylation differences associated with nutritional intervention. Technical validation will be carried out in a sub-set (10%) of samples using pyrosequencing. Significant hits will be those with *p* value <0.05 after correction for multiple testing. For the cross-tissue analysis, correlations of blood versus buccal methylation will be assessed using Pearson correlations.

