#### Other analyses

To gain insights into underlying mechanisms, gene pathways analysis will be performed for the intervention-methylation-outcome genome wide association analysis. We will compare results from the intervention-methylation, methylation-outcome, and pathways analyses between the cohorts to identify commonalities and differences and explore further opportunities for meta-analysis. We will examine potential single nucleotide polymorphism (SNP) effects on methylation through methylation Quantitative Trait Loci (mQTL) analysis using the genome-wide genotype data on the children. We will also consider options for performing causal analysis with generated genotype data using Mendelian Randomisation (MR) [27–29].

DNA methylation assays for the discovery sample of Mumbai children and all of the Gambian children are scheduled to be completed in late 2017. Assays for the replication sample of Mumbai children will be completed in early 2018. The full EMPHASIS analysis (Stages 1 and 2) will be completed by mid-late 2018.

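### The aim is epigenetic mediation, but the listed analyses test its two links separately, and the one causal step (Mendelian randomization) is firm in the abstract and optional in the methods

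*Protocol article*

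**What the plan says.** The abstract states that the study "will investigate epigenetically mediated links between peri-conceptional nutrition and health-related outcomes in children". The Background section expects that "the distinct methylation patterns identified will show potentially causal associations with phenotypic characteristics in the children", and its Context subsection argues for follow-up of randomised trials as "reducing the problems of confounding and bias that affect observational studies, thus providing stronger evidence of causality".

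The analyses listed are these:

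- **Stage 1** (Data analysis): allocation against methylation, in each cohort separately.
- **Stage 2**: Stage 1 hits, together with every candidate locus, "will be tested for associations with phenotype data measured in the children at the time of DNA collection". Newborn measurements and gestation are tested in the same way. A further hypothesis-free scan relates methylation to outcomes.
- **Other analyses**: pathways, cross-cohort comparison, mQTL, and possibly MR.

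On MR the abstract says "Causal mechanisms for nutrition-methylation-phenotype associations will be explored using Mendelian Randomization". Other analyses says "We will also consider options for performing causal analysis with generated genotype data using Mendelian Randomisation (MR". The Discussion describes mQTL as instruments in two-sample MR.

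The Data analysis section also points to a detailed analysis plan on the study website, which is not at hand.

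**The concern.** Randomisation protects the allocation-methylation link and would protect an allocation-phenotype comparison. It does not protect the methylation-phenotype link. Methylation is measured in the same children at the same follow-up as the childhood phenotypes, and years after the birth outcomes, so Stage 2 is observational.

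A locus can therefore respond to the supplement and also correlate with a phenotype without lying on the path between them. There are two routes: a shared cause of methylation and phenotype, or an allocation effect on the phenotype that bypasses the locus. The listed analyses do not separate either route from mediation unless MR is carried out and is feasible at that locus. What is at stake is whether a pair of associations is read as a nutrition-methylation-health pathway backed by a randomised design.

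**Working it through.** **1. Size of a Stage 1 hit.** The Data analysis section gives 80% power, alpha 0.05 Bonferroni-adjusted for 800,000 tests, and detectable differences of 3% (n=700) and 5% (n=293). It gives no numerical SD, so the SD is back-solved, assuming two-sided tests and 1:1 arms.

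- Alpha = 0.05/800,000 = 6.25e-8, so z = 5.411. Adding 0.842 for 80% power gives 6.253.
- SD = difference / (6.253 × √(4/N)): 6.35 points (Mumbai) and 6.84 points (The Gambia).
- Check: a common SD of 6.35 gives 3.0% and 4.64%. The second rounds to 5%, so the two stated figures agree with each other.
- Standardised allocation-methylation effect: 3/6.35 = 0.472 SD and 5/6.84 = 0.731 SD.

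**2. Shared cause, no mediation.** Simulation of 3,000 runs per setting, with no methylation effect and no allocation effect on the phenotype. Stage 1 is tested at 6.25e-8 and the rest at 0.05. The within-arm methylation-phenotype correlation of 0.16 is assumed.

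| Result | n=700 | n=293 |
|---|---|---|
| Stage 2 significant | 98.5% | 74.5% |
| Both stages significant | 77% | 58% |
| Allocation-phenotype contrast significant | 5.3% | 5.5% |
| Product-of-coefficients indirect effect significant | 99% | 76% |

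As the assumed correlation runs from 0 to 0.25, the both-stages figure runs from 4% to 79% in each cohort. The allocation contrast stays at 4–6%.

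**3. Direct allocation effect, no methylation-phenotype link within arms.** If allocation shifts the phenotype by c SD and methylation by d SD, the pooled correlation is 0.25·c·d / √[(1+0.25d²)(1+0.25c²)].

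- Mumbai, d = 0.472: c = 0.2 gives r = 0.023, and c = 0.3 gives r = 0.034.
- With n=700, r√n = 0.61 and 0.90, so a two-sided 5% test rejects in about 9% and 15%.
- Adding allocation to the Stage 2 model brings this back to about 5%.

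**4. Why an indirect effect alone does not settle it.** With a within-arm slope of 0.16 the product is 0.472 × 0.16 = 0.076 SD (Mumbai) or 0.731 × 0.16 = 0.117 SD (The Gambia), whether the slope is causal or confounded. Consider a rule that grants mediation when the indirect effect excludes zero and is compatible in sign and size with the total effect. With no true mediation it still grants the label in about 36–51% of Mumbai and 17–45% of Gambian runs (assumed correlations 0.10–0.20).

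**5. What the allocation-phenotype contrast can show.**

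- 95% CI half-width = 1.96 × 2/√n: 0.148 SD (n=698) and 0.229 SD (n=293).
- Using the birth-weight SDs in Table 1: 0.148 × 400 = 59 g and 0.229 × 417 = 95 g.
- Detectable total effect at 80% power: 0.21 SD (n=700) and 0.33 SD (n=293).
- Power for the total effects of 0.076 and 0.117 SD in step 4: about 17% in either cohort.

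**6. What MR can and cannot add.** With mQTL instruments, MR addresses methylation to phenotype. It does not test whether the supplement changed the phenotype. It also needs a genetic instrument at the locus. The Discussion treats genotype-independent variation as evidence that a nutrition-associated locus is a metastable epiallele, and such a locus would lack an mQTL instrument.

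**The case against.** A reader might infer that the article treats passing both stages as proof of mediation. It does not. The Background section states the main objectives as to "identify methylation differences associated with the interventions and correlate these with health-related phenotypes in the children", Stage 2 is labelled as associations, and the Discussion concedes difficulty over the direction of causality for birth outcomes. That objection stands, and the point is limited to what could be read into the results.

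A reader might also infer that the plan has no causal analysis. That is wrong too: MR is named, and it targets the methylation-phenotype confounding at issue. What remains is that its status differs between abstract and methods, and that it leaves the supplement-to-phenotype question untouched.

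The article condenses a fuller plan, and model form and covariates may well be there. That stands for model detail. It does not cover the choice of which relationships to test, which the article does set out and which does not match the aim.

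The allocation effect on birth weight is already reported in the article. In Mumbai there was no intention-to-treat difference, and +48 g (p = 0.05) in the per-protocol group from which EMPHASIS draws its sample. In The Gambia there was no significant effect. This stands, so the gap concerns the childhood phenotypes and how the birth-weight results will be set beside any methylation-birth weight hit.

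Finally, the simulated rates depend on assumed confounding, and they score one locus against one phenotype without covariates or multiplicity correction in Stage 2. That also stands.

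**Conclusion.** The point holds in a limited form. The aim is worded as mediation and justified by randomisation, but the listed analyses test two links separately and do not use the allocation-phenotype contrast. MR is a commitment in one place and an option in another. A confounded or direct-effect chain could therefore be read as mediated.

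Under an assumed confounded correlation of 0.16, both stages pass in 77% and 58% of runs with no mediation. A direct allocation effect of 0.2–0.3 SD raises false Stage 2 hits to 9–15%. These figures rest on the assumed correlations, linear models, 1:1 allocation and the back-solved SD. They show that the two stages cannot tell the explanations apart, not how often this will happen.

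The allocation-phenotype contrast keeps its error rate at about 5% when there is no effect, but it bounds strong chains only. A null contrast should not be taken as disproof of mediation.

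**What to change.** For each intervention-associated locus taken into Stage 2:

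1. Report the allocation-phenotype effect with its 95% CI beside the methylation-phenotype result. For birth weight, cite the parent-trial results.
2. Include allocation in the Stage 2 model.
3. Make the abstract and Other analyses agree on whether MR will be done.
4. Describe the results as two associations unless a pre-specified causal analysis supports mediation.

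A product-of-coefficients indirect effect may be added only with a sensitivity analysis for mediator-outcome confounding. It should not by itself license the word mediated, because it carries the same confounding as Stage 2.

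The cost is plan wording and modest extra analysis, since allocation and phenotypes are already recorded. The price is that fewer loci can be described as mediators, and that the allocation contrast will be imprecise, most of all in The Gambia.

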**Fig. 4 Fig4:**
[figure not shown]
Stage 2 Associations of intervention-associated DMRs and loci with health outcomes

**Fig. 5 Fig5:**
[figure not shown]
Associations of methylation and outcomes

**Table 4 Tab4:** Phenotypic outcomes in the children in both cohorts

Domain	Primary outcomes	Secondary outcomes
Birth outcomes	Measured:	Measured:
	Birth weight (g) Birth length (cm)	Head, chest, abdomen and mid-upper arm circumferences (cm) Triceps and subscapular skinfolds (mm)
	Derived**:** Small for gestational age (SGA, N [%])^a^	Derived**:** Gestational age (weeks) Low birth weight (<2500 g) (N [%]) Pre-term (<37 completed weeks’ gestation) N [%])
At follow-up in childhood		
Anthropometry	Measured**:**	Measured**:**
	Standing height (cm)	Weight (kg) Sitting height (cm) Head, chest, waist, hip and mid-upper arm circumferences (cm) Biceps, triceps, subscapular, supra-iliac skinfolds (mm)
	Derived**:**	Derived**:**
	Body mass index (BMI) (kg/m^2^) Weight-, height- and BMI-for-age Z-scores^b^ (SD)	Stunted, wasted, underweight^b^ (N [%]) Leg length (cm) Sitting height/leg length ratio Head circumference-for-age Z-score^b^ (SD) Sum of skinfolds (mm) Waist/hip ratio Longitudinal growth measures
Body composition (DXA**)**	Measured:	Measured:
	Total lean mass (kg) Total fat mass (kg)	Android fat (kg) Gynoid fat (kg)
	Derived: Lean mass index (kg/m^2^) Fat mass index (kg/m^2^)	Derived: Body fat %
Bone (DXA and pQCT)	Measured:	Measured:
	*DXA:* Total and spine bone area (BA) (cm^2^) Total and spine bone mineral content (BMC) (g) Derived: *DXA:* Spine bone mineral apparent density (BMAD; (g/cm^3^)	*DXA:* Total and spine bone mineral density (BMD) (g/cm^2^) *pQCT (Gambia only):* Metaphyseal (8%) and diaphyseal (50%) tibia. Measurements taken using voxel size 0.5 mm, slice thickness 2 mm. Tibial total and trabecular BA (mm^2^) and volumetric BMD (vBMD) (mg/mm^3^). Diaphysial BA (mm^2^), BMC (mg/mm), vBMD (mg/mm^3^), cortical area (mm^2^) and thickness (mm), and strength (cross-sectional moment of inertia) (mm^4^).
Cardio-metabolic risk markers	Measured:	Measured:
	Systolic blood pressure (mmHg) Fasting glucose (mmol/l) 30- &120-min glucose (mmol/l) LDL-cholesterol (mmol/l) HDL-cholesterol (mmol/l) Triglycerides (mmol/l)	Diastolic blood pressure (mmHg) Fasting insulin (pmol/l) 30-min insulin (pmol/l)
	Derived:	Derived:
	Insulin resistance (HOMA-IR)^c^ Disposition index^d^	High blood pressure (mmHg)^e^ Insulinogenic index^f^ Metabolic syndrome N [%])^g^
Cognitive function	Measured:	
	Scores from Atlantis, Pattern reasoning, Kohs block design, Word order, Verbal fluency and Coding tests	
	Derived**:**	
	Mental processing index^h^ (SD)	

**Legend:**
^a^ SGA defined as below the 10th percentile for birth weight for gestational age using INTERGROWTH data [51]

^b^ according to WHO/CDC growth reference: http://www.who.int/growthref/en/

^c^ Insulin resistance according to Homeostasis Model Assessment: https://www.dtu.ox.ac.uk/homacalculator/

^d^ Disposition index: an estimate of insulin secretion taking into account insulin resistance, to be calculated as insulinogenic index/HOMA-IR [52]

^e^ High blood pressure defined as >99th percentile according to an international reference: https://www.nhlbi.nih.gov/health-pro/guidelines/current/hypertension-pediatric-jnc-4/blood-pressure-tables

^f^ Insulinogenic index: an estimate of first-phase insulin secretion, calculated as (insulin at 30 min – fasting insulin)/(glucose at 30 min – fasting glucose) [53]

^g^ Metabolic Syndrome: There is no accepted definition of metabolic syndrome in children of this age; a binary variable will be created, where 1 represents children who are above the highest sex-specific within-cohort quartiles for android fat on DXA, systolic blood pressure, plasma triglyceride concentration and HOMA-IR, and below the lower quartile for HDL-cholesterol

^h^ a composite score of cognitive function, calculated as the mean of the standardised scores from the 6 individual cognitive tests

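### The metabolic syndrome outcome requires the worst quartile on all five markers at once, so it is likely to be too sparse to be informative, especially in The Gambia

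*Protocol article*

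**What the plan says.** Table 4 of the protocol article lists metabolic syndrome as a derived secondary outcome in the cardio-metabolic domain. Note g of the legend gives the rule: "There is no accepted definition of metabolic syndrome in children of this age; a binary variable will be created", with the value 1 for "children who are above the highest sex-specific within-cohort quartiles for android fat on DXA, systolic blood pressure, plasma triglyceride concentration and HOMA-IR". Those are four criteria. A fifth, for HDL, is attached with the same conjunction: "and below the lower quartile for HDL-cholesterol". No phrase such as 'any of' or 'at least three of' qualifies the list. I take 'above the highest quartile' to mean above the upper quartile cut point, which matches the wording used for HDL.

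Under Data analysis, Stage 2, intervention-associated loci and all candidate loci "will be tested for associations with phenotype data measured in the children at the time of DNA collection". The power paragraph in the same section assumes a "sample size of 700 in the Indian cohort and 293 in The Gambia". The article gives no expected prevalence, case count or power for this outcome.

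**The concern.** External cut-offs can give a high frequency in a high-risk population. Sex-specific within-cohort quartiles cannot: each criterion is met by about a quarter of children, however healthy or unhealthy the cohort is. The frequency of the composite then depends only on how strongly the five markers cluster. Requiring all five at once can leave almost no children coded 1.

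This is the only planned variable that measures clustering of the metabolic markers. If it has a handful of cases, a null result says nothing about clustering, and a comparison between the two cohorts has little meaning when one of them may have between none and four cases.

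**Working it through.** The article states no figure for this outcome, so there is none to reproduce.

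**Inputs from the article.** Five criteria, each with marginal probability 0.25 (Table 4, note g). N = 700 and 293 (Data analysis, power paragraph). The Abstract gives a larger Mumbai total: "1100 children aged 5–7 y in MMNP and 298 children aged 7–9 y in PMMST".

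**Assumptions.** The article gives no correlations between the markers. I use a five-variate normal with a common correlation r, all markers signed in the adverse direction, and show a range. Data are taken as complete on all five markers, so for a given r the expected counts are upper figures.

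**All five criteria.** Under independence, p = 0.25^5 = 0.00098. For r > 0, with c = 0.674 (the normal 75th percentile),

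p = ∫ φ(t) · [Φ((√r·t − c)/√(1 − r))]^5 dt.

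Expected cases are N·p, and the probability of no case is (1 − p)^N.

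| r | p | Cases of 700 | Cases of 293 | P(no case), 700 / 293 |
|---|---|---|---|---|
| 0 | 0.098% | 0.7 | 0.3 | 51% / 75% |
| 0.1 | 0.35% | 2.4 | 1.0 | 9% / 36% |
| 0.2 | 0.81% | 5.7 | 2.4 | 0.3% / 9% |
| 0.3 | 1.5% | 10.6 | 4.4 | <0.1% / 1% |
| 0.4 | 2.5% | 17.4 | 7.3 | <0.1% / 0.1% |
| 0.5 | 3.8% | 26.4 | 11.1 | <0.1% / <0.1% |

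An illustrative unequal correlation matrix (0.05 to 0.35) gives 0.81%, or 5.6 and 2.4 cases, the same as r = 0.2. With all 1100 Mumbai children, the expected cases are 1.1 at r = 0, 8.9 at 0.2, 16.7 at 0.3 and 41 at 0.5.

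**What such counts can detect.** With m cases, the methylation difference in SD units detectable with 80% power at an unadjusted two-sided alpha of 0.05 is (1.960 + 0.842)·√(1/m + 1/(N − m)).

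- 7 of 700: 2.802·√(1/7 + 1/693) = 1.06 SD.
- 3 of 293: 2.802·√(1/3 + 1/290) = 1.63 SD.
- 26 of 700 (r = 0.5): 2.802·√(1/26 + 1/674) = 0.56 SD.
- 11 of 293 (r = 0.5): 2.802·√(1/11 + 1/282) = 0.86 SD.

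For comparison, an even split gives 2.802·√(2/350) = 0.21 SD for 700 and 2.802·2/√293 = 0.33 SD for 293. Any multiplicity correction makes all of these larger.

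**Other readings of the rule.**

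- At least three of five, independence: 10·0.25³·0.75² + 5·0.25⁴·0.75 + 0.25⁵ = 0.0879 + 0.0146 + 0.0010 = 10.4%, or 72 and 30 cases.
- At least three of five, r = 0.3: 17.0%, or 119 and 50 cases.
- Any one of five, independence: 1 − 0.75⁵ = 76%, which would not describe a syndrome.

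**The case against.** The strongest reply is that little depends on this variable. Systolic pressure, HDL-cholesterol, triglycerides and HOMA-IR are continuous primary outcomes in Table 4, and android fat is a continuous secondary outcome. The cardio-metabolic question is therefore examined with full information whatever happens to the composite. The article also says openly that no accepted definition exists at this age. This stands, and it limits the importance of the point.

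A reader might infer that the outcome cannot be analysed at all. The documents do not support that. They do not give the correlations, and at 0.4 to 0.5 there would be about 17 to 26 Mumbai cases of 700.

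A reader might also predict separation, unstable odds ratios or false positives. Those harms depend on a model, such as logistic regression with the phenotype as the dependent variable, that the article does not state. It refers to a detailed analysis plan that is not shown. Low information is the consequence that follows whichever model is used.

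A third tempting step is to extend the point to note e, "High blood pressure defined as >99th percentile according to an international reference". That is not the same defect. It is a single criterion against an external reference, so its frequency depends on how these children compare with that reference, and the article gives no figure for this. At an assumed 1% there would be about 7 and 3 cases. Across assumed prevalences of 0.5% to 5% the range is 3.5 to 35 of 700 and 1.5 to 15 of 293. A strict external cut-off is a choice, not an error shown in the text, and systolic and diastolic pressure are both listed as continuous outcomes.

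**Conclusion.** The point holds for note g. As written, the rule needs all five criteria together, and its rarity follows from the definition itself. At correlations of 0 to 0.3 it yields roughly 1 to 11 cases of 700 in India and 0 to 4 of 293 in The Gambia. At 0.5 the figures are still only about 26 and 11. The outcome is likely too sparse to be informative, especially in The Gambia. The marginal 25% is fixed by the article; the correlations and the normal model are my assumptions. If a count rule was intended, the note does not say so, and the sentence needs correcting in that case too. The primary outcomes are unaffected.

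**What to change.** Replace the binary variable in note g with a continuous score: the mean of the sex-specific within-cohort z-scores of android fat, systolic pressure, triglycerides, HOMA-IR and HDL-cholesterol, with HDL reversed. Note h already builds the cognition composite as a mean of standardised scores, so the form is familiar within the plan.

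If a binary form is kept, state that a child is coded 1 when at least three of the five quartile criteria are met. At correlations of 0 to 0.3 this gives the 72–119 and 30–50 cases shown above. On the same formula, the detectable difference at 72 of 700 is 2.802·√(1/72 + 1/628) = 0.35 SD, and at 30 of 293 it is 2.802·√(1/30 + 1/263) = 0.54 SD.

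The cost is one sentence and no new data. The downside is small: the score remains study-specific, as the current definition already is.
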